### Secondary endpoint

- Change in BMI
- Change in general metabolic indicators such as fasting blood glucose
- Changes in blood-based markers relevant to MASLD (e.g., CK18-M30, CK18-M65, PROC3, Enhanced Liver Fibrosis (ELF), NIS2+™, YKL-40, microRNA miR-34a-5p, liver-associated enzymes such as Alanine Aminotransferase (ALT), Aspartate Aminotransferase (AST), gamma-glutamyl transferase (GGT), Alkaline Phosphatase (ALP)), bilirubin levels, lipid profiles, and platelet counts.
- Gut microbiome: changes in composition
- Change in non-invasive physiological assessments linked to liver characteristics: FibroScan™ CAP value and Liver stiffness based on vibration-controlled transient elastography (VCTE)
- Change in liver fat and other surrounding abdominal organs fat through alterations in Dixon MRI sequence
- Alterations in T2* MRI measures of intestinal permeability

The efficacy parameters for the primary and secondary endpoints will involve calculating the difference between baseline visit and follow-up visit in both study arms and compare between two arms. Moreover, they will be used in calculating correlation coefficients (Pearson's or other appropriate methods) between the effect of pectin compared to placebo, adjusting for baseline values and relevant covariates such as age, sex, ethnicity and BMI. These correlation coefficients will indicate the strength and direction of the relationships between the variables.

Primary endpoint has been identified based on the results on a recent study that was conducted at University of Nottingham, showed that 4 weeks ingestion of 15-20g/day of LM pectin in healthy volunteers significantly reduced pro-inflammatory blood markers [31].

### Assessment of safety

This study is not aimed at primarily assessing safety as the study is a dietary intervention using components sourced from common foods, research team foresee no adverse reaction or side effects. Increasing fibre intake may result in bloating amongst those who have a low habitual intake of dietary fibre. However, such effects are mild and not considered as a safety concern. Those reporting having inflammatory bowel disease, those who experience irritable bowel syndrome, and those having had gastrointestinal resection surgery will not be recruited. Moreover, those with food allergies or sensitivities to components of the investigational products will not be recruited.

Pregnant and breastfeeding women will be excluded from the study because there is limited data regarding the safety of pectin and whey protein consumption during on pregnancy and breastfeeding.

The common side effect from administration of the Buscopan® (that will be used during MRI scans as antispasmodics) are very short lived (blurred vision and raised heart rate) and participants will be advised to stay at the test centre until their vision returns to normal (this normally occurs within 30 minutes of the injection). Rare side effects from administration of the Buscopan® injection include skin reactions, tachycardia, dry mouth, dyshidrosis, and in extremely rare cases angle-closure glaucoma. This will be monitored throughout the study visit at Sir Peter Mansfield Imaging Centre (SPMIC) by a registered medical doctor who will be a member of the research team and who will administer Buscopan® and monitor participants.

Mannitol 2.5% / Locust bean gum 0.2% will be used during MRI scans as oral contrast. Mannitol increases MRI contrast between the lumen and the bowel wall, and the addition of locust bean gum serves to counteract some of the recognised side effects associated with Mannitol ingestion, which can include flatulence and alteration of gastrointestinal microbiota leading to bowel spasms and diarrhoea.

### Procedures for missing, unused and spurious data

Every effort will be made within the study to minimise the occurrence of missing data. Where possible, all data available will be used.

### Definition of populations analysed

Safety set: All randomised participants who receive at least one intervention.

Full Analysis set: All randomised participants, who participated in at least one intervention and for whom at least one post-baseline assessment of the primary endpoint is available.

Per protocol set: All participants in the Full Analysis set who are deemed to have no major protocol violations that could interfere with the objectives of the study.

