### Stopping rules and discontinuation

Since the current study is a dietary intervention, research team do not foresee any adverse events. However, if a participant develops a severe adverse reaction following consumption of the supplement (i.e. severe bloating amongst those who have a low habitual intake of dietary fibre), they will be asked to contact the study team immediately. Based on the severity of the event and at the discretion of the CI, the study team may advise the participant to continue or withdraw from the study.

Moreover, participants who will agree to have MRI scans, will be carefully monitored during the scan and if their medical or physiological status alter rapidly, then it may be necessary to stop scanning based on the radiologist advice.

Participants may withdraw from the study at any point. Significant non-compliance with the study schedule may lead to a participant being withdrawn from the study.

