### Expected duration of participant participation

### Study participants will be participating in the study for 6 weeks, attending two 2 hours study visits. Participants who will agree to have MRI scans, including healthy volunteers, will need to attend two 4 hours MRI visits.

### Removal of participants from therapy or assessments/Participant Withdrawal

Participants may be withdrawn from the trial either at their own request or at the discretion of the Investigator due to safety reasons (including pregnancy) or development of severe adverse events, or due to failure to adhere to protocol requirements. The participants will be made aware that this will not affect their future care. Participants will be made aware (via the information sheet and consent form) that should they withdraw the data collected to date cannot be erased and may still be used in the final analysis. The research team will advise pregnant participants to stop the intervention and contact their GP if they have questions.

Study team will try their best to replace withdrawn participants.

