### Compliance

No interim data analyses are planned and given the simplicity of the study we will not need a data monitoring committee nor the overview of a formal study steering committee. The participant’s involvement in the study will only be terminated if the participant wishes to do so or if participants or caring clinician feel that the participants are too unwell to carry on with the study.

The study will be terminated if the participant safety is deemed to be at risk throughout the study.

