### Participant removal from the study due to adverse events

Any participant who experiences an adverse event may be withdrawn from the study at the discretion of the Investigator.

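### Participants may be withdrawn for non-adherence or adverse events before their only outcome sample, so the efficacy comparison can become one of selected week-6 completers

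*Protocol*

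**What the plan says.** **Analysis sets.** Protocol, Definition of populations analysed: the Full Analysis Set is restricted to randomised participants who received at least one intervention "and for whom at least one post-baseline assessment of the primary endpoint is available". The Per Protocol set is "All participants in the Full Analysis set who are deemed to have no major protocol violations that could interfere with the objectives of the study". The third set is for safety. The section does not say which set is the main one for efficacy.

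**Withdrawal.** Three sections give discretionary grounds:
- Stopping rules and discontinuation: "Significant non-compliance with the study schedule may lead to a participant being withdrawn from the study".
- Removal of participants from therapy or assessments/Participant Withdrawal: the investigator may withdraw someone for safety reasons "or development of severe adverse events, or due to failure to adhere to protocol requirements".
- The section on removal because of adverse events, in the Adverse Events chapter, reads: "Any participant who experiences an adverse event may be withdrawn from the study at the discretion of the Investigator".

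**Replacement.** The participant-withdrawal section adds: "Study team will try their best to replace withdrawn participants". It gives no rule on allocation, or on whether the withdrawn person stays in the analysis.

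**The opposite rule.** Under Compliance, the participant's "involvement in the study will only be terminated if the participant wishes to do so", or if the participant or the caring clinician judges the participant too unwell to go on.

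**Sampling.** The Schedule of events and the visit 2 section place study blood at baseline and week 6 only. The optional MRI visits, where blood is also drawn, fall at the same two time points. Contact in between is a weekly telephone call.

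**The concern.** Stopping the supplement and leaving the study are different events. The first is something to measure, and the second costs the outcome. The protocol lets the first lead to the second and does not ask a withdrawn participant to return for the week-6 sample. With a single post-baseline sample, withdrawal before week 6 means no outcome at all.

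Randomisation balances the arms as allocated. If withdrawal depends on adherence or tolerance, and if these differ by arm, the participants left at week 6 are no longer a randomised comparison. A difference by arm is plausible: Known Side Effects and Assessment of safety both say that extra fibre may cause bloating, and only one arm receives pectin. Replacement restores the head count but not the people who left.

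The statistical analysis plan is not at hand, but it could not repair this. No analysis rule recovers a sample that was never drawn.

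**Working it through.** **Step 1. Do the rules agree?**

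| Reason for ending participation | Stopping, withdrawal and adverse-event sections | Compliance section |
|---|---|---|
| Participant's wish | allowed | allowed |
| Too unwell | allowed | allowed |
| Adverse event short of too unwell | allowed, by discretion | not allowed |
| Non-adherence | allowed, by discretion | not allowed |

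The last two rows contradict each other.

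**Step 2. Who can enter an efficacy analysis?** The primary markers can be measured after baseline only at week 6. A post-baseline value is therefore the week-6 value, for the Full Analysis Set and for the Per Protocol set inside it. Assessment of efficacy uses the difference between the baseline and follow-up visits, which also needs the week-6 value. The mixed model under Methods could use people with baseline data only, but the set definition removes them first. Data collected before withdrawal may be kept, but before week 6 these hold no post-baseline primary marker.

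**Step 3. What can be said about size?** The protocol states no withdrawal rate, no dropout allowance and no standard deviation, so there is no figure of its own to reproduce. The one quantity that follows directly is 1/15 = 6.7% of an arm per person lost.

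The rest is illustration on assumed inputs. Suppose pectin has no true effect, 15 completers per arm are reached after replacement, and a fraction f of an arm (the least tolerant) leaves. Tolerance has correlation ρ with the marker change, and leavers are those with the worse change. The shift in an arm's mean is ρ·φ(c)/(1 − f), where c is the normal quantile at 1 − f. For f = 0.30 and ρ = 0.5: 0.5 × 0.3477/0.70 = 0.248 SD. The bias is the difference between the two arms' shifts. Type I error is from 40,000 simulated trials with a two-sided t-test at 5%.

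| Loss, pectin / control | Bias and type I error, ρ = 0.3 | Bias and type I error, ρ = 0.5 |
|---|---|---|
| 10% / 0% | 0.058 SD, 5.21% | 0.097 SD, 5.90% |
| 20% / 0% | 0.105 SD, 6.05% | 0.175 SD, 7.64% |
| 30% / 0% | 0.149 SD, 6.61% | 0.248 SD, 10.24% |
| 20% / 5% | 0.072 SD, 5.64% | 0.121 SD, 6.26% |
| 30% / 10% | 0.091 SD, 5.62% | 0.151 SD, 7.07% |

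Here the bias favours pectin. If leavers were those with the better marker change, the sign would reverse.

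**Step 4. What does keeping everyone do to the effect?** Assume an effect of 0.8 SD in completers and none in those who stop. The effect in all randomised is then 0.8 × (1 − f): 0.72, 0.64 or 0.56 SD for 10%, 20% or 30% stopping. For 80% power at two-sided 5%, n per arm = 2(1.96 + 0.8416)²/d² = 15.70/d². This gives 31, 39 or 51 per arm, against 25 for 0.8 SD. Fifteen per arm gives 80% power only for √(2/15) × 2.80 = 1.02 SD.

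**The case against.** Several stronger readings are tempting, and the documents do not support them.

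- **That the main analysis will be completers only.** Every withdrawal ground is discretionary. Someone who stops the supplement, is not withdrawn and attends visit 2 stays in the Full Analysis Set. A separate Per Protocol set presupposes violators within the full set. The protocol also does not name the main efficacy set.
- **That the schedule rule covers missed supplement.** It concerns the study schedule, and someone who misses visits may have no week-6 sample anyway. Only the wider ground of failing to meet protocol requirements clearly could reach supplement intake.
- **That tolerance does differ by arm.** The protocol says only that fibre may cause bloating and calls such effects mild. Its background section reports no recorded side effects in the healthy-volunteer pilot. That pilot differed in population and lasted 4 weeks, so it does not settle the matter.
- **That replacements refill the pectin arm.** The replacement sentence does not say so, and the randomisation sections allocate each participant by software at enrolment. Adding newly randomised participants does not by itself break randomisation.
- **That the effect is overstated by a set percentage.** With a fraction w withdrawn whose effect is k times that of completers, the gap is 1/((1 − w) + wk) − 1. It is 5% at w = 0.1, k = 0.5; 25% at w = 0.2, k = 0; and 43% at w = 0.3, k = 0. Both inputs are assumed, and replacement does not enter the formula. It is an overstatement only if the effect of assignment is the target, and the synopsis stresses mechanism.

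The protocol also promises every effort to limit missing data, and detailed handling may sit in an analysis plan. These points limit the claim. They do not remove the contradiction, the single outcome sample or the lack of any provision to collect it after withdrawal.

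**Conclusion.** The concern holds as a defect of design and wording. The withdrawal sections contradict Compliance. Followed as written, they allow non-adherent or intolerant participants to be removed before their only outcome sample, and so to drop out of every efficacy analysis. The between-arm comparison can then be one of week-6 completers selected after randomisation.

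This rests on two readings: that efficacy is analysed in the Full Analysis or Per Protocol set, and that no sample is taken at withdrawal, since none is scheduled. Bias further requires that withdrawal is related to the marker change and differs by arm. Neither its size nor its direction can be derived from the documents. The 0.06 to 0.25 SD range applies only under the assumed losses and correlations. The point should be corrected before the analysis is fixed, and preferably while week-6 samples can still be collected.

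**What to change.** 1. Reconcile the four sections (Stopping rules and discontinuation, Participant Withdrawal, Compliance, and Participant removal due to adverse events) so that they state one set of grounds. Who stops the supplement remains the investigator's decision.
2. State that stopping or missing the supplement does not by itself end study participation. Ask every randomised participant who has not withdrawn consent to attend visit 2 for the week-6 blood sample. This is the part that does the work: adding people with baseline data only to the analysis set brings little information.
3. Define the Full Analysis Set as all randomised participants in their allocated arm, including those later withdrawn, and use adherence only for the Per Protocol set.
4. State that additional recruits are added to those withdrawn, not substituted for them, and take the next random allocation.

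The cost is protocol wording and a few extra visit-2 attendances. The estimated effect will also be diluted by those who stopped. With 15 per arm that may not be slight: in the illustration, 20% stopping takes 0.8 SD to 0.64 SD and the requirement from 25 to 39 per arm.

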# ADVERSE EVENTS

### Definitions

**An adverse event is any unfavourable and unintended sign, symptom, syndrome or illness that develops or worsens during the period of observation in the study.**

An AE does include a / an:

1. exacerbation of a pre-existing illness.

2. increase in frequency or intensity of a pre-existing episodic event or condition.

3. condition detected or diagnosed after medicinal product administration even though it may have been present prior to the start of the study.

4. continuous persistent disease or symptoms present at baseline that worsen following the start of the study.

An AE does not include a / an:

1. medical or surgical procedure (e.g., surgery, endoscopy, tooth extraction, transfusion); but the condition that lead to the procedure is an AE.

2. pre-existing disease or conditions present or detected at the start of the study that did not worsen.

3. situations where an untoward medical occurrence has not occurred (e.g., hospitalisations for cosmetic elective surgery, social and / or convenience admissions).

4. disease or disorder being studied or sign or symptom associated with the disease or disorder unless more severe than expected for the participant’s condition.

5. overdose of concurrent medication without any signs or symptoms.

A Serious Adverse Event (SAE) is any adverse event occurring following study mandated procedures, having received the intervention that results in any of the following outcomes:

1. Death

2. A life-threatening adverse event

3. Inpatient hospitalisation or prolongation of existing hospitalisation

4. A disability / incapacity

5. A congenital anomaly in the offspring of a participant

Important medical events that may not result in death, be life-threatening, or require hospitalisation may be considered a serious adverse event when, based upon appropriate medical judgment, they may jeopardize the patient or participant and may require medical or surgical intervention to prevent one of the outcomes listed in this definition

Since the current study is a dietary intervention, research team do not foresee any adverse events. However, if the participant developed a severe adverse reaction to taking the allocated fibre supplement (i.e. severe bloating amongst those who have a low habitual intake of dietary fibre), they will be asked to contact the study team immediately. Based on the severity of the event and at the discretion of the CI, the study team may advise the participant to continue or withdraw from the study.

All adverse events will be assessed for seriousness, expectedness and causality:

A distinction is drawn between serious and severe AEs. Severity is a measure of intensity whereas seriousness is defined using the criteria above. Hence, a severe AE need not necessarily be serious.

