**Trial / Study Statistician:** **[name] [name]**

Professor in Genetic and Molecular Epidemiology

Surgery, Trauma and MSK Ageing

Nottingham Biomedical Research Centre,

University of Nottingham, [name]

[name]

**Trial / Study Coordinating Centre:** Nottingham Digestive Diseases Centre,

University of Nottingham, Queens Medical Centre,

[name]

SYNOPSIS

| Title | The Effect of Pectin Supplementation on Patients with Metabolic Dysfunction-Associated Steatotic Liver Disease (MASLD): A Randomised Placebo-Controlled Dietary Intervention Study |
| --- | --- |
| Acronym | PEC-MASLD |
| Short title | Pectin Supplementation and MASLD |
| Chief Investigator | [name] [name] |
| Objectives | To investigate the effects of daily pectin supplementation ingestion on pathways promoting systematic inflammation with metabolic dysfunction-associated steatotic liver disease (MASLD) enabling a better understanding of the mechanisms of action. This includes effects on gut microbiome composition, body weight, lipid metabolism, and gut and liver physiology. |
| Trial Configuration | Single centre placebo controlled randomised dietary intervention study |
| Setting | Identification of participants from secondary care setting for research across research centres: Nottingham Digestive Diseases Centre, University of Nottingham; Nottingham Clinical Research Facility at Nottingham University Hospitals NHS Trust; and Sir Peter Mansfield Imaging centre |
| Sample size estimate | The sample size was calculated using Raosoft® calculator with Confidence level of 95% ± 5% and response distribution of (50%) to know the minimum sample size. The total sample size came out to be 14 per arm. The sample size of this study is equal to 15 per arm to obtain the statistical power for the study.  This calculation was based on a previous pectin pilot study which found significant differences in 4 inflammatory markers with n=14 healthy adult volunteers. |
| Number of participants | 45 |

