**Known Side Effects**

As this is a dietary intervention trial using widely available foodstuffs consumed as advised by manufacturers, no serious adverse events/side-effects or ethical issues are expected. Participants will be given the details of the trial supplements - those with food allergies or sensitivities to components of the foods/components will not be recruited. Increasing fibre intake may result in bloating amongst those who have a low habitual intake of dietary fibre. However, such effects are mild and not considered as a safety concern. Presence of inflammatory bowel disease, irritable bowel syndrome, and gastrointestinal resection surgery are exclusion criteria for the study to avoid exacerbating these conditions. Pregnant and breastfeeding women will be excluded from the study because there is limited data regarding the safety of pectin and whey protein consumption during pregnancy and breastfeeding.

The common side effect from administration of the Buscopan® (that will be used during MRI scans as antispasmodics) are very short lived (blurred vision and raised heart rate) and participants will be advised to stay at the test centre until their vision returns to normal (this normally occurs within 30 minutes of the injection). Rare side effects from administration of the Buscopan® injection include skin reactions, tachycardia, dry mouth, dyshidrosis, and in extremely rare cases angle-closure glaucoma. This will be monitored throughout the study visit at Sir Peter Mansfield Imaging Centre (SPMIC) by a registered medical doctor who will be a member of the research team and who will administer Buscopan® and monitor participants.

Mannitol 2.5% / Locust bean gum 0.2% will be used during MRI scans as oral contrast. Mannitol increases MRI contrast between the lumen and the bowel wall, and the addition of locust bean gum serves to counteract some of the recognised side effects associated with Mannitol ingestion, which can include flatulence and alteration of gastrointestinal microbiota leading to bowel spasms and diarrhoea.

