**Dietary intervention (6 weeks):**

Control and intervention arms: Each participant will be randomly assigned to either pectin with whey protein and cocoa powder or control whey protein with cocoa powder using online software (sealedenvelope.com) to determine intervention A or B at enrolment. Randomisation will ensure equal distribution of key characteristics that might confound between-group comparisons and will be evaluated using baseline data analysis. Participants in the intervention arm (N=15) will be required to take 15g of pectin combined with 15g of unflavoured whey protein powder and 5g of cocoa powder as a flavour per day for a period of 6 weeks. The participants in the placebo/control arm (N=15) will be required to take 30g of unflavoured whey protein powder combined with 5g of cocoa powder as a flavour per day for the same period of 6 weeks. All supplements will be provided, pre-weighed, in food grade pouches and will be given sufficient cover the total intake for the 6-weeks period. Participants will be asked to incorporate the supplement provided in 250-300ml of water taken once at morning or evening. Regular weekly contact will be made via phone calls by [name] to record patients’ feedback or any adverse event that might occur due to ingestion of supplements and to ensure participants receive any information that becomes available during the course of the research that may be relevant to their continued participation .

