**Healthy Volunteers MRI Scans**

Both healthy volunteers MRI scans visits will be arranged at the Sir Peter Mansfield Imaging Centre (SPMIC). The participant will attend the visit fasted. The MRI research team will use Philips 3T MRI scanner. The team will firstly scan the hepatic fat and other surrounding GI organs fat using Dixon MRI sequences. Then, a medical doctor, who is a member of the University of Nottingham research ream, will cannulate the participant, take a blood sample from the participant and will ask them to drink the oral contrast which consists of 2.5% Mannitol and 0.2% Locust Bean Gum and will be prepared by MRI research team at the SPMIC on the morning of the scan. The participant will be asked to drink the oral contrast gradually over 40 minutes. This contrast required to provide contrast between the lining of the gut and its contents. After that, the medical doctor will prescribe and administer hyoscine butylbromide (Buscopan®) through the cannula while MRI research team taking T2* MRI measures of gut wall to measure gut permeability. Buscopan® is used to stop the bowel moving to allow the team to generate clear pictures of the bowel wall.

The medical doctor will confirm eligibility and document this, prior to performing any research activity related to the cannulation/administration of hyoscine butylbromide (Buscopan®).

Each MRI scans visit will take around 4 hours.

It is extremely unlikely that MRI scan will show any abnormality. Even if there were an abnormality, it is unlikely that research team would notice it since we are taking these MRI scans for scientific research, so they are not the same as scans collected by doctors for medical purposes. Furthermore, the pictures will not be looked at by a radiologist.

If the research team did find anything abnormal on the MRI scan, the investigator would arrange for an appropriately qualified doctor, from a healthcare provider e.g. a NHS Trust or a private doctor, to look at them. That specialist doctor would contact participant GP to explain the situation, so that participant GP could then advise them.

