## Trial Intervention Related SAEs

**A serious adverse event that is unexpected in its severity and seriousness *and* deemed directly related to or suspected to be related to the trial intervention shall be reported to the ethics committee that gave a favourable opinion as stated below.**

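### The SAE definition, causality scale and REC trigger hang on an undefined term, and the safety set on randomisation, so serious events from the MRI agents are not clearly covered

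*Protocol*

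**What the plan says.** - **SAE definition** (Protocol, Adverse Events, Definitions). An SAE "is any adverse event occurring following study mandated procedures, having received the intervention that results in any of the following outcomes". The paragraph that follows the list of outcomes calls the study a dietary intervention and gives, as the reaction of concern, one to the allocated fibre supplement.
- **Causality** (Protocol, Causality). All four grades are framed around administration of the trial intervention. An event that other treatments, chemicals or disease plausibly explain falls in the lowest grade and counts as unrelated for notification.
- **REC reporting** (Protocol, Trial Intervention Related SAEs). The trigger is an unexpected SAE "deemed directly related to or suspected to be related to the trial intervention shall be reported to the ethics committee". The Chief Investigator's seven-day report has the same relatedness condition.
- **Safety population** (Protocol, Definition of populations analysed). "Safety set: All randomised participants who receive at least one intervention".
- **Exposure outside the supplement** (Protocol, Healthy Volunteers MRI Scans; MRI visit 1 and 2). At each MRI visit, volunteers and consenting patients are cannulated, drink the mannitol and locust bean gum contrast, and receive intravenous Buscopan.
- **Named risks** (Protocol, Known Side Effects). For Buscopan: blurred vision, raised heart rate, skin reactions and, extremely rarely, angle-closure glaucoma. For mannitol: effects "which can include flatulence and alteration of gastrointestinal microbiota leading to bowel spasms and diarrhoea". For the supplement: mild bloating.

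**The concern.** The formal safety rules are written around the shake, while the more notable risks the protocol names come from the MRI agents. Healthy volunteers receive those agents twice and never take the shake.

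If the rules are applied literally, a volunteer admitted to hospital after Buscopan or contrast might not meet the SAE definition. The event might be graded unrelated because something other than the supplement explains it, and so not go to the REC. It would not appear in any table built on the safety set. The grading problem also reaches randomised patients having the optional MRI. At stake are correct classification and onward reporting of serious events, and a safety summary that covers everyone exposed.

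**Working it through.** **Participant total.** The synopsis gives "Number of participants | 45". The Dietary intervention section has 15 in the pectin arm and 15 in the control arm. Recruitment of healthy volunteers has 15 volunteers, each scanned twice.

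15 + 15 + 15 = 45, which reproduces the stated total and shows that the protocol counts volunteers as participants.

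**Share outside the safety set.** Volunteers are not randomised: 15 / 45 = 33%.

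**Planned exposures to Buscopan plus contrast.**
- Volunteers: 15 × 2 = 30.
- Patients: the scans are optional, so from 0 to 30 × 2 = 60. Uptake is not stated, and 60 is a ceiling rather than a forecast.

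**The four rules under two readings of *intervention*.** No formula applies here. The question is what each rule does with a serious reaction to an MRI agent.

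| Rule | Narrow reading: the supplement | Broad reading: includes the scans |
|---|---|---|
| SAE definition | Volunteer: receipt condition never met. Patient: not met if the baseline-day scan comes before the first dose | Met |
| Causality scale | Buscopan or mannitol is an other treatment or chemical, so the event can be graded unrelated | Can be graded related |
| REC trigger | Not reached if graded unrelated | Reached if the event is also unexpected |
| Safety set | Volunteer excluded | Volunteer still excluded, because randomisation is required |

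**Which reading does the text support?** The paragraph after the SAE definition points to the narrow one. The synopsis points the other way, since it describes the volunteer scans in the row on interventions. The Informed consent section uses the word more loosely still, for physical examination and history taking. The term has no definition, so the first three rules are ambiguous. The fourth excludes volunteers on either reading.

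**Patients.** The first scan is arranged for the baseline day, when the supplement is dispensed, so it may come before any dose. After dosing starts, the receipt condition is met, but the causality scale still allows an MRI-agent reaction to be put down to another treatment and counted as unrelated.

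**The case against.** The strongest reply is that these people have real safety cover.

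- A registered doctor, who also gives the Buscopan, monitors participants throughout the MRI visit (Known Side Effects; Assessment of safety). Everyone scanned is monitored during the scan (Stopping rules and discontinuation).
- The section on expected duration treats volunteers as participants. The adverse event definition covers the whole period of observation and includes conditions found after a medicinal product is given.
- All adverse events are to be assessed, recorded and followed. Participants are asked to contact the site about any serious event, and the Chief Investigator is told of any SAE (Reporting of adverse events).
- The SAE sentence also names study procedures. The clause on important medical events allows an SAE classification on medical judgement without repeating the receipt condition.
- Analysis populations serve the randomised comparison, and the protocol says safety is not its primary aim. A separate MRI table could be left to a statistical analysis plan.

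Most of this stands. It rules out a reading that a reader might reach, namely that volunteers fall outside safety monitoring. It also means that exclusion from the SAE and REC rules is a risk of ambiguous wording rather than an established fact.

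It does not remove the point. General recording does not settle whether an event is an SAE, is related, or goes to the REC, and those rules should not depend on which sense of a word the reader picks. As for the safety set, the protocol does not leave it open: it fixes a definition that excludes volunteers.

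A reader might also infer that delayed contrast effects would be missed after the last scan. The documents do not support this, because they give no onset time for mannitol's effects. It is true that the weekly calls concern "any adverse event that might occur due to ingestion of supplements" and that no call after a volunteer's scan is described. Whether to add one is a choice about intensity of follow-up; no contradiction in the protocol requires it.

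**Conclusion.** The point holds as a defect of wording and scope that should be fixed; it does not show that safety oversight is absent.

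- **Certain:** the safety set leaves out 15 of 45 participants (33%), who account for 30 planned exposures to Buscopan and contrast.
- **Dependent on the reading:** under the narrow sense of *intervention*, serious events from Buscopan, contrast or cannulation may fail the SAE definition in volunteers, and in patients scanned before their first dose. In any scanned participant they may be graded unrelated and not reach the REC. Under the broad sense they are covered.

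The figures assume the planned numbers are recruited and every volunteer completes both scans. Patient exposures lie between 0 and 60, depending on uptake.

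**What to change.** 1. **Definitions (Adverse Events):** define an SAE as an adverse event with a listed outcome that occurs after any study product or study-mandated procedure (supplement, oral contrast, Buscopan, cannulation). Delete prior receipt of the intervention as a condition.
2. **Causality and Trial Intervention Related SAEs:** grade and report relatedness to the supplement or to any study procedure or agent, so that an MRI agent is no longer an alternative explanation that makes an event unrelated. The expectedness condition can stay as it is.
3. **Definition of populations analysed:** define the safety set as all participants who receive any study product or MRI agent. Tabulate healthy volunteers separately from the randomised arms, and MRI-agent events separately from supplement events.

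The cost is amended wording in these sections and slightly more events to classify and tabulate. No dose, procedure, visit or sample size changes.
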